### Sample size

The appropriate sample size is determined by the non-inferiority approach and was calculated for the primary outcome measure ‘Social Functioning Scale’ [46, 47]. This scale has been used in a subsample of a randomised Housing First trial, from where the necessary data has been taken [48]. For calculating the appropriate sample size of the RCT study site, the application ‘Power and Sample Size’ [49] was used applying the following parameters: Power: 0.9; significance level: 0.025; non-inferiority margin: 15; difference between treatments (group means): 111.2–106.7; standard deviation: 12; and allocation ratio: 1:1. This procedure yielded a sample size of 28 people to be included in each arm.

The OSD sample size is based on the calculation for the RCT. Thus, 28 participants will be included in the treatment arm. For propensity scoring, the many-to-one matching method was chosen. Here, it is recommended to have a 2–3 times larger control group to facilitate matching [50, 51]. Accordingly, 56 to 84 participants will be included in the control group.

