At both study sites, service users are considered to be intent-to-treat (ITT) after using their respective residential rehabilitation service for at least one month. Participants not considered to be ITT due to withdrawal before one month will be excluded from the study. If participants leave their residential rehabilitation setting after using it for at least one month, assessments with participants will continue in order to investigate the further progress of residential service users. Each dropout occurring during the recruitment phase will be replaced by a new subject in order to ensure an adequate number of participants in in each condition according to the power analysis. In case of dropout, all corresponding data on the contact sheet will be deleted and the person will never be contacted again. However, study data assessed before will be retained. Recruitment is complete when the intended number of participants is reached, after 21 months’ recruitment period at the latest. For the methodological objective, every participant at both study sites will be asked to consent for further use of data in encrypted form.

All assessed data will be entered in REDCap [53]. Participants will be coded and no personal data will be disclosed. The assessors of each study site will store personal data in password-protected files in order to contact them for conducting the assessments on a drive of the university.

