## Data analyses

Relevant packages of the statistical software R will be used for conducting all statistical analyses [71]. For analysing and reporting, we follow the CONSORT guidelines for the reporting of non-inferiority and equivalence randomised trials [72, 73]. The main analyses will be performed using an a priori statistical analysis plan. For all analyses, Bonferroni corrections will be applied where necessary.

Missing data is expected due to refused items, missed appointments and drop-outs. With regard to recommended sensitivity analyses of missing data, we state the following assumptions about missing data: Missing data due to refused items is assumed to be independent of the respective treatment condition and to be completely related to the items refused. Thus, they are assumed to be missing at random (MAR). Due to the preference probably inherent in the investigated interventions and the associated difficulties [32, 37], missing data due to dropouts has to be assumed to be missing not at random (MNAR). Missing data will be analysed and imputation methods applied if appropriate [74, 75].

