### Primary objective: care-related goal

For analysing the primary outcome variable social inclusion we will check for non-inferiority both in per-protocol and in imputed ITT samples to assess the security of inference of non-inferiority as recommended in the CONSORT guidelines for non-inferiority trials [72, 73].

Primary analysis will compare primary and secondary outcomes between IHS and RCS/TAU after 6, 12 and 24 months separately for both study sites. A repeated measure approach will be used where indicated. Non-inferiority of IHS compared to RCS/TAU will be accepted based on a 2.5% significance level if the lower bound of the 97.5% CI of M_IHS_-M_RCT/TAU_ is > δ = − 15, and vice versa, non-inferiority of IHS compared to RCS/TAU cannot be accepted if the lower bound of the 97.5% CI of M_IHS_-M_RCT/TAU_ is ≤ δ = − 15. This non-inferiority margin corresponds to one standard deviation of 15 scale scores (*m* = 100; *SD* = 15) on the primary outcome variable SFS [46, 47] and was chosen based on the clinical judgment of experts as no RCT investigating the SFS as outcome measure in a comparable sample was available [81]. In addition, assay sensitivity will be analysed by investigating pre-post differences in a first step. Assay sensitivity will be assumed, if there is a statistically and clinically significant pre-post increase in the SFS total scale score [82].

All other outcome measures will also be tested on their non-inferiority using the definition of margin δ as one standard deviation of the respective scale. Analyses will be extended to superiority testing in case of confirmed non-inferiority, and to interaction terms to explore mechanisms of treatment effects.

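### At the RCT site, 28 per arm gives 90% power only with complete outcome data, and replacing dropouts during recruitment cannot protect that number at 24 months

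*Protocol article*

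**What the plan says.** All references are to the Protocol article.

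- **Sample size.** The inputs are "Power: 0.9; significance level: 0.025; non-inferiority margin: 15", then "difference between treatments (group means): 111.2–106.7", a standard deviation of 12 and 1:1 allocation. The result is "This procedure yielded a sample size of 28 people to be included in each arm". No loss rate or inflation is mentioned, and the abstract gives 56 to be randomised, which is 2 × 28. The observational (OSD) treatment arm takes over the 28; its control group is set at 56 to 84.
- **Participant recruitment.** "Each dropout occurring during the recruitment phase will be replaced by a new subject in order to ensure an adequate number of participants"; the sentence goes on to tie that number to the power analysis. The end of recruitment is also fixed: "Recruitment is complete when the intended number of participants is reached, after 21 months’ recruitment period at the latest". Personal contact data of dropouts are deleted and they are not approached again. People who leave their housing after at least one month are still assessed.
- **Outcome assessment and measures.** Visits are at baseline and at 6, 12 and 24 months.
- **Primary objective.** The comparison is made at 6, 12 and 24 months, separately by site.
- **Data analyses.** "Missing data is expected due to refused items, missed appointments and drop-outs". Dropout is assumed to be missing not at random. The Challenges section names attrition bias as the main difficulty of the RCT.

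**The concern.** The only provision for keeping the number of participants at the powered level is replacement, and it ends when recruitment ends. The 24-month outcome is one of the three primary time points, and every 24-month visit comes after that end. A participant who drops out after recruitment closes is neither replaced nor recoverable. Replacements enrol late themselves, so most of their own follow-up is also uncovered.

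At stake is how the power figure is read. The article gives one figure, 90%, and says that replacement serves to hold the number behind it. A reader who meets an inconclusive 24-month RCT result could take it to come from a comparison with 90% power when fewer than 28 per arm supplied data.

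**Working it through.** **1. Inputs.** From Sample size: margin 15, difference 111.2 − 106.7 = 4.5, SD 12, power 0.9, significance level 0.025. The section states neither sidedness nor the direction of the difference. The stated 28 is reproduced with a one-sided 0.025 and the 4.5 points taken against IHS. A two-sided 0.025 gives 33, a zero difference gives 14, and 4.5 points in favour of IHS gives 8. The one-sided reading fits the decision rule, which uses the lower confidence bound only. The distance to the margin is therefore 15 − 4.5 = 10.5.

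**2. The plan's own figure.**

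n per arm = 2 × 12² × (1.960 + 1.2816)² / 10.5² = 27.45, rounded up to 28.

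The stated figure is reproduced, and nothing has been added for loss. (A t-based calculation gives 29, a trivial difference.)

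**3. Timing.** Recruitment runs from April 2019 to December 2020, 21 months at most. The first participant's 24-month visit is April 2021 at the earliest, after closure. Because 24 > 21, this holds for any accrual pattern. Someone enrolled in December 2020 is followed to December 2022 with no possible replacement. With even accrual over the full 21 months, 12/21 = 57% of 12-month visits also fall after closure. That is a share of visits, not a loss rate.

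**4. Power by number observed.** Normal approximation: power = Φ(10.5 / (12 × √(2/n)) − 1.960).

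For n = 28: 12 × √(2/28) = 3.207; 10.5 / 3.207 = 3.274; 3.274 − 1.960 = 1.314; Φ = 0.906.

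| Observed per arm | Normal | t |
|---|---|---|
| 28 | 90.6% | 89.5% |
| 27 | 89.5% | 88.4% |
| 24 | 85.8% | 84.3% |
| 22 | 82.7% | 80.9% |
| 20 | 79.0% | 76.9% |

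There is almost no slack: losing one person per arm takes the normal-approximation figure below 90%.

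**5. Power by assumed loss.** The article gives no rate, so these are assumptions (normal approximation, same fraction lost in both arms, none replaced):

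- 10%: 28 × 0.9 = 25.2 per arm, power 87.4%
- 20%: 22.4 per arm, power 83.4%
- 30%: 19.6 per arm, power 78.2%

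With loss in the control arm only, 28 against 20, power is 84.8% (t: 83.3%).

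**6. OSD site, same inputs, ignoring the effect of matching.** Power = Φ(10.5 / (12 × √(1/n₁ + 1/n₂)) − 1.960).

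- 28 against 56: 10.5 / 2.777 = 3.780, power 97%
- 28 against 84: 10.5 / 2.619 = 4.010, power 98%
- After 30% loss in both groups, 20 against 39: 89%; 20 against 59: 92%

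**The case against.** The strongest reply is that the article makes no claim about power at 24 months. Sample size attaches the 90% to no time point, and the replacement sentence states its own limit openly: it speaks of dropouts in the recruitment phase and gives a purpose, not a guarantee. This stands. A reader might infer that the article promises 90% at 24 months and breaks the promise. The text does not say that. What it does is give one power figure for a comparison made at three time points, and offer in support of the required number a safeguard that cannot reach the last of them.

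Further points also have weight:

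- **The loss is assumed.** With no loss after closure, 90% would hold. But the article itself expects dropouts, particularly in the RCT control group.
- **The figures are for an unadjusted two-group comparison at one visit.** The plan foresees repeated measures where indicated, and imputation. As an illustration, if baseline adjustment were used and the baseline–outcome correlation were 0.5 (an assumption), the SD would fall to 12 × √0.75 = 10.39, and power would be about 92% at 22 per arm and 89% at 20. Imputation does not restore the information of 28 observed outcomes, least of all when dropout is assumed to be missing not at random.
- **The 4.5-point deficit is demanding.** At a true difference of zero, power is about 98% even with 20 per arm. The stated 90%, however, is calculated at the deficit.
- **Attrition is managed.** People who leave their housing are still assessed, and RCT participants are paid for each assessment. Both reduce loss, but neither helps with those who end contact.
- **The decision rule is sound.** A failed test means that non-inferiority cannot be accepted, not that IHS is inferior, and the interval width would show lost precision.

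Loss scenarios may also sit in the full protocol or analysis plan, so their absence from the article is not the point. The point is the unqualified 90% next to a replacement rule said to secure it.

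**Conclusion.** The point holds for the RCT site, as a matter of how the power is stated. Two parts are certain from the article alone: 28 per arm is the complete-data requirement, and replacement cannot cover any loss after recruitment closes, so no 24-month visit is protected by it. The size is conditional: roughly 3 to 12 percentage points below the 90.6% for losses between 10% and 30%, under an unadjusted comparison, a true 4.5-point deficit and no recovery through modelling.

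Two stronger readings are not supported. One is that the trial is shown to be underpowered at 24 months; without a loss rate, and with adjustment possible, that cannot be said. The other is that the same shortfall applies at the OSD site; with 56 to 84 controls it starts at about 97–98% and stays near 90% even after 30% loss. This is a minor point that does not call the design into question.

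**What to change.** - **Sample size:** state that 28 per arm gives 90% power when all 28 have outcome data, and give the expected 24-month RCT power under a stated loss assumption, together with the analysis model assumed.
- **Participant recruitment:** limit the replacement sentence so that it is said to maintain numbers only for losses that occur before recruitment closes.

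Both changes are wording. They need no extra enrolment and no change to the analysis. The cost is a less favourable stated power for the RCT at 24 months.

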### Interventions

The study intervention called Independent Housing and Support (IHS) is a psychosocial residential rehabilitation programme and means direct placement of people with SMI in accommodation in the community, i.e., without prior housing arrangements. This complex intervention follows the “First place – then train” paradigm which is well-known from Supported Employment within vocational rehabilitation. The accommodation is usually a flat rented at service user’s choice, and is financed at their expense. The service user will be supported by an off-site residential coach concerning all aspects related to finding and keeping his or her accommodation, including contacts with the landlord, social environment, relatives, and administration. The residential coach will not be in charge of any issue related to treatment or therapy, but will cooperate with the service user’s psychiatrist or psychiatric service. The intensity of residential coach support will be flexible and according to the service user’s needs. IHS is not transitional, but permanent and without time limitation and is independent of therapy or care. The main goal is the social inclusion of service users.

The control condition RCS/TAU consists of traditional residential care settings (RCS) such as staffed or unstaffed care homes, shared or non-shared apartments rented by the residential agency, and other treatment as usual conditions (e.g. host families, unsupervised living). RCS settings are part of a continuum of residential services other than hospital for non-acute support that aim to enable the individual with SMI to live independently. Users live in a group in a single or shared room, and receive daily support on-site or at least 7 h per day and at least on 5 days per week. If there is no continuous support on-site, users get 24 h on-call support. The hiring contract is concluded with the residential agency. In some of the RCS settings, there is the expectation that users will move on within two years. Closed residential settings or traditional housing settings not fulfilling the above criteria will be excluded from the present study.

As both study conditions are part of psychiatric rehabilitation not providing any acute psychiatric care, temporary inpatient or outpatient stays in a (mental) hospital are seen as common and will neither affect their utilisation of the rehabilitation setting nor their participation in the study.

### Outcome assessment and measures

Participants will be followed for two years after enrolment. Outcome assessments take place at baseline (T0), after 6 months (T1), 12 months (T2) and after 24 months (T3). Data will be collected by interview with participants as well as by self-report questionnaires answered by participants in a paper-pencil format. Assessments with participants will be conducted by trained assessors at the participants’ accommodation or another place of their choice. Model fidelity as well as the costs of RCS/TAU will be assessed by interview with heads of each of the utilised residential rehabilitation service.

Social inclusion will be assessed as the primary outcome as the main goal of residential rehabilitation approaches is the social inclusion of individuals with SMI. Secondary outcomes include functioning, quality of life, mental state, diagnoses, needs, capabilities, life events, social support, service utilization and costs. Participants’ diagnoses as well as contact frequency in IHS settings are collected from clinical records. All outcome measures will be assessed with a German version of the corresponding measures.

#### Social inclusion

The *Social Functioning Scale* (SFS) [46, 47] was developed specifically for adults with SMI and is used as the primary outcome measure to assess participants’ social inclusion. The 76-item questionnaire consists of seven subscales assessing participants’ social engagement/withdrawal, interpersonal behaviour, independence-performance, independence-competence, recreation, pro-social activities, and employment/occupation. Most of the items are to be answered on a 4-point Likert scale, and higher scores indicate better social inclusion. Raw total score range between 0 and 135 and each subscale score can be translated in scale scores with *m* = 100 and *SD* = 15. The German version showed good internal consistency and high validity and turned out to be comparable with the original English version [47].

#### Functioning

Participants’ functioning will be rated with the *Health of the Nation Outcome Scales* (HoNOS) [54] and with the modified scale of the *Global Assessment of Functioning Scale* (m-GAF) [55]. The HoNOS includes twelve items to be rated on a 5-point Likert scale. Total score range between 0 and 48, with lower score as indicator for better functioning. The German version of the rating scale (HoNOS-D) showed satisfactory feasibility, reliability and validity for most of the items [56, 57]. The m-GAF measures illness severity based on psychopathology and functioning on a 1 to 100 scale with higher score as indicator for better functioning. When possible, functioning will be rated by participants’ key workers, or by study collaborators when that is not possible (e.g. in some control condition situations or after the utilisation of IHS).

#### Mental state

For assessing mental state, the 9-item *Symptom Checklist* (SCL-K-9) [58] questionnaire will be used. Findings of its evaluation indicate the SCL-K-9 to be a suitable and efficient instrument for screening psychopathologic symptomatology with mostly satisfactory psychometric properties [59]. The questionnaire asks mental health problems on a 5-point Likert scale resulting in a total-score range from 0 to 36, with lower score implying better mental state.

#### Service utilisation

The evaluation of the German adaptation of the *Client Sociodemographic and Service Receipt Inventory* (CSSRI-EU) [61] proved its feasibility in assessing utilisation of mental health care in Germany. A study-specific adaptation to mental health care and residential rehabilitation settings in Switzerland (CSSRI-CH) will be used to measure costs and utilization of psychiatric services. The nine items ask participants for 1) their main source of income, 2) their net income in Swiss Francs, 3) their whereabouts in the last 12 months, 4) any health care utilisation for physical health problems and 5) for mental health problems, 6) any intake of psychotropic medication, 7) contact with criminal justice services, 8) internet access, and 9) any other support utilised. Evaluation will be conducted in a descriptive manner.

#### Support

For assessing emotional social support, the German adaptation of the *ENRICHD Social Support Inventory* (ESSI-D) [62, 63] will be utilised. The ESSI-D consists of five items to be answered on a 5-point Likert scale between “never” and “always” and proved to be an economic instrument with good reliability and satisfactory construct validity to assess emotional support in a sample of heart disease patients.

Additionally, 20 individual questions will be used to ask about important life events in the past six months, possibilities of self-determination, satisfaction with housing aspects, emotional and social support.

#### Needs

The *Camberwell Assessment of Need – Short Appraisal Schedule* (CANSAS) [64, 65] will be applied for assessing participants’ needs concerning 22 domains of health and functioning. The needs are ascertained by interview and rated on a 3-point scale (no problem; met need; unmet need). For interpretation, the met and unmet needs each will be summed-up. Inter-rater and test-retest reliability as well as validity showed to be reasonable to good [64], the psychometric properties of the German version were satisfactory [65].

#### Capabilities

The *Oxford Capabilities Questionnaire – Mental Health* (OxCAP-MH) [66, 67] is a 16-item questionnaire assessing participants’ capabilities on a 5-point Likert-scale. Total score ranges from 16 to 80 and can be translated into standardised score ranging from 0 to 100, with higher score indicating better capabilities. The scale shows good applicability as well as good validity and reliability [66, 67].

#### Service provision and costs

The mean number and duration of contacts with service users in IHS will be assessed with the Swiss medical tariff reimbursement tool (TARMED) that is currently the basis for outpatient reimbursement. This tool also allows to calculate the costs of service utilisation. Because TARMED only is used by the IHS settings, heads of each RCS/TAU service will be asked by a single item for the daily or weekly costs of their service during the fidelity assessments (see below).

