## Methods

### Aims of the study

Based on these findings, we aim to investigate both 1) a care-related and 2) a methodological goal with the current multi-centre study to answer the following research questions:
What are the effectiveness and efficiency of IHS compared to RCS/TAU for non-homeless persons with severe mental illness after 6, 12, and 24 months?Do the RCT and the OSD yield similar results?

The primary objective is to evaluate the effectiveness and efficiency of IHS and to directly compare it to traditional RCS/TAU for non-homeless people with severe mental illness. Effectiveness will be determined by social inclusion, proposed as a key outcome for individuals living with mental disorders and, in terms of research, a global priority measure [45]. Efficiency will be analysed based on the costs associated with the service utilization of the different housing settings. As the political goal is seen in allowing a freedom of choice in where to live and which support services to utilise [3] and because the differences in outcomes of previous studies between IHS and RCS for non-homeless populations were only small or inexistent [16, 19–22], we utilise a non-inferiority hypothesis in our study. We hypothesize that IHS yields no poorer social inclusion outcomes than traditional RCS/TAU.

One study centre is going to conduct an OSD with propensity score matching methods and the other center plans to conduct an RCT while learning from the results of the recently failed feasibility trial of IHS [4]. Thus, to our knowledge, the present study will include the first RCT investigating housing conditions for non-homeless people with SMI. The secondary objective of this study is to directly compare the outcomes of the RCT with the OSD. Here, we utilise the hypothesis that the OSD will provide similar results to the RCT. If the hypothesis is confirmed, observational studies investigating residential rehabilitation programmes for the non-homeless population could be considered as equivalent to the RCTs so far solely conducted with respect to homeless people.

In addition, we will conduct secondary analyses to investigate the moderation, mediation and procedural factors in IHS and RCS/TAU that influence outcomes.

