## Discussion

There is a strong preference in service users for independent living but a considerable lack of research into housing services in the context of mental health. In this prospective, four-arm cohort study we aim to evaluate the effectiveness and efficiency of Independent Housing and Support (IHS) compared to institutionalised residential care settings and other treatment as usual conditions (RCS/TAU) for people with SMI in two cities in Switzerland. Effectiveness will be assessed by social inclusion and related outcomes while efficiency will be analysed by service usage and costs testing hypotheses of non-inferiority. Participants will be enrolled between April 2019 and December 2020 and assessed at baseline, after six, twelve and after 24 months. At one study site, 56 participants will be randomly assigned to one of the conditions; the other study site will use an observational study design including 112 participants.

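### Housing support is costed by non-equivalent methods in IHS and RCS/TAU, and what the RCS/TAU figure covers is not defined

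*Protocol article*

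**What the plan says.** The protocol article makes efficiency part of the primary objective (Aims of the study): "Efficiency will be analysed based on the costs associated with the service utilization of the different housing settings". Outcome assessment and measures lists service utilisation and costs among the secondary outcomes.

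Service provision and costs fixes two sources for the cost of housing support. For IHS, contacts and their duration are taken from TARMED, from which costs are then calculated. TARMED is used only by the IHS settings, so for the comparator "heads of each RCS/TAU service will be asked by a single item for the daily or weekly costs of their service". That question is put during the fidelity interviews, which Model Fidelity schedules per service: once when recruitment opens there, and again a year after the final participant has been recruited.

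Interventions describes the accommodation. The IHS flat is rented by the user "and is financed at their expense". For RCS, "The hiring contract is concluded with the residential agency". The control condition also takes in host families and unsupervised living.

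Service utilisation adds the CSSRI-CH, asked of participants in both conditions. One of its nine items covers "their whereabouts in the last 12 months". The section closes: "Evaluation will be conducted in a descriptive manner". The Discussion, by contrast, says that "efficiency will be analysed by service usage and costs testing hypotheses of non-inferiority". Visits are at 0, 6, 12 and 24 months.

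**The concern.** A cost comparison needs the same components, valued from the same perspective, on both sides. Here one side is built up per person from support contacts at a tariff. The other is a single figure per service, which does not vary with the support a resident receives. Lodging is outside the first by construction and may or may not be inside the second. For a control participant in unsupervised living there may be no head of service to ask.

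The abstract ties the policy conclusion to non-inferiority in both effectiveness and efficiency, so a cost difference that partly reflects who pays for the room would carry weight. It could not be repaired at analysis: if neither the lodging share nor the rent is collected, no statistical analysis plan can separate them later.

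**Working it through.** The article gives no cost values, so there is no figure to reproduce. The check sets out what each source measures, then compares the recall window with the visit schedule.

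**1. What the two sources yield.** Let S be support cost and L lodging cost per person, with subscripts I (IHS) and R (RCS/TAU). Let k be 1 if the head of service includes lodging and 0 if not.

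- IHS as measured: S_I (TARMED contacts; user-paid rent is outside).
- RCS/TAU as measured: S_R + k·L_R.
- Measured difference, IHS minus RCS/TAU: (S_I − S_R) − k·L_R.

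Error of the measured difference (measured minus target) for three possible targets:

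- Support costs only, target S_I − S_R: error −k·L_R. It is zero if k = 0 and leans towards IHS if k = 1.
- Total costs whoever pays, target (S_I − S_R) + (L_I − L_R): error (1 − k)·L_R − L_I. If k = 1 it is −L_I, leaning towards IHS. If k = 0 it is L_R − L_I, of open sign.
- A payer who funds RCS lodging but not IHS rent, target (S_I − S_R) − L_R: error (1 − k)·L_R. It is zero if k = 1 and leans against IHS if k = 0.

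The article states neither k nor the target, so the direction cannot be settled.

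**2. Whether another instrument fills the gap.** The CSSRI-CH items as listed are income source, net income, whereabouts, physical and mental health care, psychotropic medication, criminal justice contact, internet access and other support. None is described as recording rent.

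**3. Could rent matter in scale?** This is illustration only; every input is an assumption. Take 1 to 4 contact hours a week, CHF 150 to 200 an hour, rent of CHF 800 to 1,500 a month, and 4.345 weeks a month.

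- Low contact cost: 1 × 4.345 × 150 = CHF 652 a month. With rent of 1,500: (652 + 1,500) / 652 = 3.3.
- High contact cost: 4 × 4.345 × 200 = CHF 3,476 a month. With rent of 800: (3,476 + 800) / 3,476 = 1.2.

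Under these assumptions, including rent multiplies the IHS figure by about 1.2 to 3.3. This shows that the scope of the cost can matter; it does not estimate a bias in this study.

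**4. Recall window.** A 12-month item asked at month v covers v − 12 to v:

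- T0: −12 to 0
- T1: −6 to 6
- T2: 0 to 12
- T3: 12 to 24

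At T1, 6 of 12 months (50%) precede enrolment. T1 and T2 overlap by min(6, 12) − max(−6, 0) = 6 months. T2 and T3 do not overlap and together cover months 0 to 24 exactly. If the conditions differ by D per month after enrolment and not before, the T1 window shows (6 × 0 + 6 × D) / 12 = D/2 per month.

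**The case against.** A reader might infer that the comparison favours IHS by construction. The documents do not support that. The item asks for the costs of the service; it does not call this a price or say that the bed is included. The sentence on the hiring contract names the contracting party, not who bears the rent, and RCS users may pay rent too. From a payer's perspective, leaving out user-paid rent can be legitimate. A missing or zero cost for controls in unsupervised living leaves the direction open or makes controls look cheaper. All of this stands, and it removes any claim of an established direction.

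The CSSRI-CH also captures other service use in both conditions, so the asymmetry is confined to housing support. That stands.

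A reader might also take the recall window as further evidence of a lean towards IHS. It is not. It is stated for one item, is the same in both conditions, and dilutes a 6-month contrast. Its use at every visit is itself inferred. Double counting arises only if T1 and T2 are added, which the article does not propose.

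Costing perspective and methods often sit in a fuller protocol or the analysis plan, and Data analyses refers to such a plan. That answers a complaint about missing detail. It does not answer the point here: the article itself fixes two unlike data sources, and a later plan cannot recover components that were not collected.

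On the wording conflict, the descriptive statement concerns the CSSRI-CH, the other is a Discussion summary, and Limitations calls secondary-outcome analyses exploratory. The tension is real but minor.

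**Conclusion.** The concern holds in a limited form. The housing-support component, which feeds an efficiency question within the primary objective, is costed by non-equivalent methods. The RCS/TAU figure has no defined scope and may not exist for part of the control condition. If that figure includes lodging, a comparison of support costs or of total costs leans towards IHS. This is plausible for a residential service but not established, and no size can be derived from the documents. The result on the Social Functioning Scale is unaffected.

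The T1 recall mismatch is a separate, smaller point: half the window precedes enrolment, assuming that the 12-month wording is used at that visit. The exact halving of the monthly contrast also assumes no difference between conditions before enrolment. The descriptive and non-inferiority statements need only be reconciled.

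**What to change.** 1. At the head-of-service interviews, ask for the daily or weekly cost split into support and lodging/board. The second interview is already scheduled, so services interviewed before the change can still supply the split.
2. Record rent paid by IHS users and by controls who have no service to report a cost, for example beside the CSSRI-CH income items.
3. State one costing perspective, apply the same components to both conditions, and report support costs alone and total costs.
4. At T1, ask about whereabouts since the last interview, or leave T1 out of cumulative costs and use T2 plus T3.
5. Align the Service utilisation section and the Discussion on whether service use and costs are described or tested for non-inferiority.

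The cost is two or three extra items, slightly longer interviews and some changes of wording. The main drawback is that service heads must estimate the lodging share, so that split will carry some error.
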